### Sample size calculation

The sample size for the baseline survey is calculated based on the method suggested by the WHO STEPWISE Approach [22]: for our study, we calculate 884 participants with 20% non-response. A systematic random sampling method will be performed as a sampling technique. For the power calculation, we took reference from a quasi-experimental study from Nigeria that reported an effect size of 5% between intervention and control group during a 13-week period [23]. We expect an effect size of 10% increase in our study with a 1-year follow-up where FCHVs are mobilized to conduct home visit counseling once every 3 months and the intervention takes place in an ongoing community-based program for non-communicable diseases from 2014 [16]. Assuming, 20% loss to follow-up and ICC of 0.01 and seven clusters per arm will provide 90% power resulting to 49 women per cluster. The total sample size needed for the intervention study is 690 that will be recruited from the 884 participants (baseline survey), which is enough to obtain 90% power.

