**Methods:**

A community-based, open-label, two-armed, cluster-randomized trial [seven clusters (geographical wards) randomized for the intervention, and seven for the control arm]. The participants are recruited from a population-based survey with a sample size of 884. Based on population proportion size, 277 women will be recruited for the intervention group and 413 women recruited for the control group. A 12-month community-based health education intervention will be administered mobilizing the FCHVs, based on the Health Belief Model. The primary outcome measure of the study will be the difference in percentage of cervical cancer screening uptake between the two study arms. The primary outcomes will be modeled by using mixed-effect logistic regression analysis.

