### Study design and setting

The proposed trial is a community-based, 12-month, open label, two-arm cRCT with an equal allocation of clusters (geographical wards) between intervention and control arms in a semi-urban area of Pokhara Metropolitan city (former Lekhnath municipality, administratively divided in to 15 wards). It is one of the two areas where the Cervical Cancer Screening and Prevention (CCSP) pilot program was first initiated in Nepal. The total population of Lekhnath municipality is 59,498 (female 32,104 and male 27,394) with the total number of households being 14,958 as per the 2011 census [18]. Each ward will be considered as one cluster. Although the study area is composed of 15 clusters, only 14 will be selected for the cluster randomization (one cluster that is comparatively different from others in socio-demography and health service availability is excluded). Allocation of the clusters into intervention and control arms is described below. The study area is limited to health services comprising one recently upgraded 25-bedded hospital from a primary health care center, three health posts, and six urban health care centers. According to the District Public Health Office, Kaski in 2018, there were 123 FCHVs in the municipality.

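### The stated 90% power was derived for 49 women in every ward, but the trial recruits 277 against 413, and the control uptake, alpha and test behind the figure are not given

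*Protocol article*

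**What the plan says.** All of the power inputs that the article gives stand in the Sample size calculation section:

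- Effect: "We expect an effect size of 10% increase in our study with a 1-year follow-up". No pair of rates is given.
- Loss, clustering and number of wards: "Assuming, 20% loss to follow-up and ICC of 0.01 and seven clusters per arm".
- Result: "seven clusters per arm will provide 90% power resulting to 49 women per cluster".
- Claim for the total of 690 women: "which is enough to obtain 90% power".

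The abstract then allocates the 690 in proportion to population: "277 women will be recruited for the intervention group and 413 women recruited for the control group". The Randomization section allocates wards 1:1, so there are seven wards in each arm.

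The Data analysis section plans a mixed-effect logistic regression of screening within one year. Neither section states an alpha, sidedness or reference distribution for the power figure. The only uptake figures in the article are in the Background: 2.8%, 1.5% and 5.4%, each for a different age band.

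**The concern.** The figure of 49 per ward implies 7 × 49 = 343 women per arm and 686 in all. The planned arms are 277 and 413, so the intervention arm is 66 women (19%) below 343 and the control arm is 70 above it. The article carries the 90% over to the total of 690 as though only the total mattered. It does not. The intervention arm has the higher expected uptake and so the larger binomial variance, and it is the smaller arm.

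Two further features make the figure hard to rely on. For a fixed absolute difference, power depends strongly on the control rate, which is missing. And with 14 randomised wards the between-arm comparison has about 12 degrees of freedom, while the article does not say whether the calculation allowed for this.

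At stake is how a null result is read. A reader will take it as coming from a trial with 90% power for a 10-point effect, when that figure was not computed for the design being run.

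**Working it through.** **Inputs from the article.** Seven wards per arm; 49 per ward (calculation) or 277 and 413 per arm (recruitment); 20% loss; ICC 0.01; effect of 10%.

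**Assumptions.** The 10% is 10 percentage points; alpha is 0.05 two-sided; wards are of equal size within an arm; the control rate p0 is varied, with p1 = p0 + 0.10.

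**Formulas.** With m women analysed per ward, the design effect is DE = 1 + (m − 1) × 0.01 and the effective n per arm is 7m/DE. SE² = p1(1 − p1)/n1 + p0(1 − p0)/n0.
- Normal, unpooled: power = Φ(0.10/SE − 1.96).
- Normal, pooled: the same, with the critical value applied to the pooled-variance SE.
- t: non-central t on 12 df, noncentrality 0.10/SE, critical value 2.18.

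**Step 1: reproduce the stated figure.** m = 49 × 0.8 = 39.2; DE = 1 + 38.2 × 0.01 = 1.382; effective n = 274.4/1.382 = 198.6 per arm. At p0 = 5.4%, power is 91.1% (unpooled) or 90.7% (pooled). Exactly 90% is reached at p0 = 5.9% (unpooled; 5.88% before rounding), 5.7% (pooled) or 4.0% (t). The stated 90% is therefore reproducible, but only with a back-solved control rate that depends on the test.

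**Step 2: put in the recruited arms.**
- Intervention: 277/7 = 39.6 per ward; m = 31.7 after loss; DE = 1.307; effective n = 169.6.
- Control: 413/7 = 59.0 per ward; m = 47.2; DE = 1.462; effective n = 226.0.

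Worked example at p0 = 5.88%: SE² = 0.1588 × 0.8412/169.6 + 0.0588 × 0.9412/226.0 = 0.000788 + 0.000245 = 0.001033. SE = 0.0321 and 0.10/SE = 3.11. Normal unpooled power = Φ(3.11 − 1.96) = 87.5%.

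| Test assumed for the 90% | p0 at which 49 per ward gives 90% | Power with 277/413, same test |
|---|---|---|
| Normal, unpooled | 5.9% | 87.5% |
| Normal, pooled | 5.7% | 89.7% |
| t, 12 df | 4.0% | 87.1% |

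The split alone costs about 0.3 to 3 points.

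**Step 3: separate the split from the number of wards** (p0 = 5.88%).

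| | Normal, unpooled | t, 12 df |
|---|---|---|
| 49 per ward | 90.0% | 84.5% |
| 277/413 | 87.5% | 81.5% |

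If the plan used a normal test, the move to t costs about 5.5 points with equal wards. That is more than the split costs.

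**Step 4: vary the control rate** (277/413, ICC 0.01).

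| p0 | Normal, unpooled | Normal, pooled | t, 12 df |
|---|---|---|---|
| 1.5% | 97.2% | 98.1% | 94.4% |
| 2.8% | 94.8% | 96.0% | 90.8% |
| 5.4% | 88.7% | 90.4% | 82.9% |
| 6% | 87.2% | 89.0% | 81.1% |
| 10% | 77.9% | 79.6% | 70.8% |

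**Step 5: vary the ICC** (277/413, t on 12 df). The values above 0.01 are assumptions.

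| p0 | ICC 0.01 | ICC 0.02 | ICC 0.03 |
|---|---|---|---|
| 2.8% | 91% | 84% | 77% |
| 6% | 81% | 72% | 64% |

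**The case against.** The strongest reply is that the discrepancy is small and that the rest comes from the reviewer's choices. Much of this stands.

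- **The split is not what brings power to 81%.** A reader might infer that recruiting 277 against 413 cuts power from 90% to 81%. It does not: under a normal test the split leaves 87.5–89.7% at the implied control rates. The 81% also needs a control rate near 6% and a change from a normal to a t reference.
- **The normal test is an inference.** If the planners already used t on 12 df, the implied control rate is 4.0%, and 277/413 gives 87%. The article cannot settle which they used, and a small-cluster correction in the analysis may be left to an SAP.
- **The design can still reach 90%.** At two of the article's three uptake figures it does so even with t (94% at 1.5%, 91% at 2.8%). A claim that 90% needs control uptake of about 3% or less is true only for the t reference.
- **High control uptake is not established.** The setting is described thus: "It is one of the two areas where the Cervical Cancer Screening and Prevention (CCSP) pilot program was first initiated in Nepal". A reader might infer uptake above 5.4%, but no local rate is reported, and the outcome concerns screening within the trial year, for which the article gives no control figure. The 10% row is a sensitivity case, not a forecast.
- **The recruitment margin is not a finding.** From "we calculate 884 participants with 20% non-response" one might compute 884 × 0.8 = 707 interviews, which is tight for 690. But 884 may be the number already inflated for non-response, or the number surveyed, and the Trial status section says accrual is closed.

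What the reply does not remove is that the 90% was derived for 343 per arm and is claimed for 277 and 413, with the inputs needed to check it left out. Under each of the three tests, at the control rate that makes 49 per ward yield 90%, the recruited arms yield less.

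**Conclusion.** The power statement is wrong as written, by a modest amount. Taken on its own terms, it overstates power by about 0.3 to 3 points because of the 277/413 split. If it also rests on a normal test, a 12-df reference brings power to about 81–83% at 5.4–6% control uptake. Across control rates of 1.5–10% with t and ICC 0.01, power runs from 94% to 71%, so the missing control rate matters more than either correction.

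These figures assume a 10-point absolute effect, two-sided alpha of 0.05, 20% loss in both arms and equal ward sizes within each arm. Unequal ward sizes would lower them slightly: an assumed coefficient of variation of 0.3 takes 81.5% to about 80.6%.

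The article does not support a single replacement figure of 81%, nor the statement that the chance of missing the effect is double what is claimed. Severity is minor to moderate.

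**What to change.** Rewrite the power paragraph for the design being run:

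1. State the control rate (and its source), that the effect is an absolute 10 points if that is meant, alpha with sidedness, and the test used.
2. Recompute for 277 and 413 women before 20% loss, in 7+7 wards, with a t reference on 12 df. Use actual ward sizes if they are to hand.
3. Replace the claim that 690 is sufficient for 90% with the result, or with a short range over control rates of 1.5–10% and a few ICC values from 0.01 upwards. With t and ICC 0.01 that range is 94% to 71%.

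Do not print 81% as the single answer, since it fixes a control rate and a test that the article does not state. Enrolment, allocation and the planned regression stay as they are. The cost is one paragraph of wording and a power claim that depends openly on its assumptions.

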### Interventions

After randomization, the FCHVs in intervention wards will receive training coordinated by the research team in collaboration and close supervision of the local health authority. The training manual is designed under the guidance of experts in cervical cancer and public health from the national and international organizations. The training manual is based on the following: training of community health workers, WHO, 2017 training manual [24] and Cervical Cancer Screening and Prevention (CCSP) A Reference Manual 2015 [25]. The FCHVs will receive a 3-day training package highlighting: (a) an introduction to NCDs and cervical cancer, (b) cervical cancer causes and risk factors, (c) cervical cancer screening and service availability, (d) providing health education and counseling women (30–60 years), and (e) recording, reporting, and follow-up. An overview of program content is presented in Table 1. Educational sessions are guided by the use of the Health Belief Model [26], and training materials will be reviewed and validated by experts and major stakeholders. The developed training materials will be pretested with the FCHVs from a nearby area not included in the study. In addition, the FCHVs will also receive health education materials (pamphlets), referral cards, and a recording register during the training session.

**Table 1 Tab1:** Session plan for FCHV training

Day	Session	Main contents
**Day 1**		
	Introduction to non-communicable diseases (NCD)	What is NCD and its situation in Nepal? What are the different types of NCDs? What are the risk factors for NCDs? How can we prevent NCDs?
	Cervical cancer Causes and symptoms	Have you ever heard of cancer? What is cancer? What is cervical cancer? What causes cervical cancer? What are the symptoms of cervical cancer? How does the community perceive cervical cancer?
	Discussion	Questions/answers and doubt clearance
	Evaluation	First day evaluation and FCHV selection
**Day 2**		
	Cervical cancer Causes and symptoms	What causes cervical cancer? What are the symptoms of cervical cancer? Human papilloma virus and it’s transmission Who are at risk of having cervical cancer?
	Cervical cancer screening and prevention	What to do to prevent cervical cancer? What are the different types of screening methods? Visual inspection with acetic acid (VIA) What is the recommended age group for VIA screening? Who does the VIA screening? Service delivery points and cost Role of FCHV to prevent cervical cancer Myths about VIA screening.
	FCHV home visit	Planning for home visit Number of visits and timing Rapport building Reason for the visit and the health education session Recording, reporting
	Interactive learning	Flip chart topics FCHV posture, body language, preparedness, proactive towards the situation, voice Detailing the flip chart
**Day 3**		
	Recording register	Explain the content of the recording register How to prepare and fill the recording register? Name, age, location of the participants and FCHV Submission of completed register to the research officer
	Pamphlet	Explain the content of the pamphlet How to stress the points in the pamphlet What to suggest to the participants who are not able to read the pamphlet?
	Referral card	Explain the content of the referral card How to fill the referral card? Name, age, location, and health facility address for referral Communication with the health facility
	Scenario planning	Role play
	Household selection and list preparation	Selection of the household for home visit according to FCHVs working area.

At the end of the training, FCHVs will assign the number of households that have to be visited based on the baseline survey. Participants in the intervention clusters will receive a 12-month, home-based, health education package administered by FCHVs in a household setting. FCHVs will visit each household, meet the selected participant, receive approval, and provide the health education. On average, one FCHV will meet 18 participants three times a year. FCHV will complete the three visits to provide health education even if the participants have already received VIA screening. During the visit, FCHVs will deliver the health education intervention, to encourage and empower women for cervical cancer screening uptake available free of cost at their local health facility. They will also conduct two reinforcement visits every 4 months from the first visit (three home visits in a year).

Health workers conducting cervical cancer screening at the local health facility in the intervention group will receive orientation about the study to make sure that the women attending the health facility receive screening. They will ensure that the equipment is functional and reagents are available, record information, provide psychosocial counseling to the case positives, and refer for further confirmation and treatment. The recorded information at the health facility will be tallied using the referral slip to confirm women’s participation for cervical cancer screening. The collected data will be kept strictly confidential and will only be accessed by the members of the trial team.

Each participant is assigned an individual trial identification number, which is securely stored. The principal investigator reserves the right to the data set and could share upon reasonable request.

There will be no special criteria for discontinuing or modifying allocated interventions. Furthermore, the implementing community-based intervention for cervical cancer screening uptake will not require alteration to usual care pathways (including use of any medication) and will continue for both the trial arms.

A field supervisor will routinely visit each FCHV in order to maintain motivation and collection of records from the health facilities. The supervisor also provides ad hoc help to the FCHVs when needed during the intervention period. We will also use a supervision checklist to track and update the knowledge and skill levels of FCHVs as well as to ensure fidelity to the study protocol.

In the control clusters, participants will receive “usual care.” The usual care means the current health education and promotion practices for cervical cancer screening at the community level provided by the government health system. They will not receive further contact, information, or educational materials from FCHVs until the 12-month assessment.

### Minimization of contamination

The risk and level of contamination will be monitored at the levels of FCHVs and participants. FCHVs will be instructed not to share information about the study and not to provide any support to people from other clusters in the community, other than the ones who are assigned. The risk of contamination will also be minimized by the cluster design, whereby the intervention and control clusters will be geographically separated and the chance of intervention cluster participants regularly meeting control cluster participants will be negligible. All possible means of contamination between intervention and control participants will be collected during the follow-up survey and adjustments will be made for estimating the effect.

### Intervention fidelity

The intervention is designed under the guidance of experts in cervical cancer and public health from the national and international organizations. The subject experts and major stakeholders reviewed and validated the training materials. The education session were delivered under the close supervision of the local level health authority and the research team, who will monitor the intervention. The Data Safety and Monitoring Board (DSMB) along with a member from the Nepal Health Research Council will evaluate the progress of the trial, including periodic assessments of data quality and timeliness, participant recruitment, accrual and retention, participant risk versus benefit, performance of the trial site, and other factors that can affect study outcome. Each FCHV in the intervention cluster will be advised of the importance of following the intervention steps and content during the training session. The field supervisor will monitor FCHVs tasks. FCHVs will deliver the services guided by a register that keeps them reminded of stages of the intervention and will report every 4 months.

### Data analysis

STATA version 15 software (StataCorp, College Station, TX, USA) will be used for quantitative analysis following the Consolidated Standards of Reporting Trials (CONSORT) guidelines for cluster-randomized trials. Flowcharts (Fig. 1) will include the number of participants seen at each stage of the trial, eligible, randomized, and analyzed for the primary outcome. In the initial analysis, we will compare baseline characteristics of enrolled participants in the study arms and follow-up status. We will use mixed-effect logistic regression to compare between the groups as the outcome (the primary outcome would be the difference in the proportion of women who participate in the cervical cancer-screening program between intervention and control within 1 year). Comparison of the knowledge scores between baseline and follow-up, after 1-year intervention, will measure the knowledge level. Estimation will take into account the effect of potential confounders (age, ethnicity, education, parity, income, location, etc.).

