### Randomization

Clusters will be randomly assigned to intervention and control areas using a 1:1 allocation ratio. Randomization will be done before the participants are recruited. Research teams responsible for identifying potential participants, obtaining consent, and recruiting trial participants will be blinded to the participants’ allocation status. The following steps will be taken to avoid selection bias during random allocation: (a) clusters will be randomized only after the baseline survey, (b) clusters will not be withdrawn from or added to the study, and (c) a statistician from abroad who is not familiar to the study will randomize the clusters.

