### Outcomes

#### Primary and secondary outcomes

The primary outcome of the study is percentage change in cervical cancer screening uptake from baseline to follow-up in the intervention group compared to the control group in a 12-month home-based health education intervention. The baseline survey will be conducted before the cluster randomization, and a follow-up survey of similar method will be conducted after 12-month intervention. The response of each participant for cervical cancer screening in the baseline survey and the follow-up survey will be compared to evaluate the percentage. In addition, FCHV will provide a referral slip to the participants in the intervention group (keeping a copy of the referral slip to submit to the field supervisor) during the home visit, which they take with them and submit to the health facility for VIA screening. The referral slip contains study code, name, age, address, and signature of both FCHV and the participant. FCHV will inform the participants about the health facility where the services are freely available. The key health personnel providing the VIA screening services are oriented about the study. Furthermore, confidentiality about the participants’ information will be maintained throughout the intervention. The field supervisor will collect the referral slip to confirm that the participants have received VIA screening and results from all the health facilities of the intervention ward as a reference to the participants’ response.

The secondary outcomes of the study are change in the level of knowledge and awareness among women on cervical cancer screening and prevention. The response of each participant for knowledge and awareness on cervical cancer screening in the baseline survey and the follow-up survey will be compared to evaluate the change using the validated questionnaire [19, 20].

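### The primary mixed logistic model for 14 wards has no stated small-sample method and no stated route to the difference in percentage; a ward-level t analysis supplies both cheaply

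*Protocol article*

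**What the plan says.** The abstract describes "seven clusters (geographical wards) randomized for the intervention, and seven for the control arm", and the Randomization section confirms it: "Clusters will be randomly assigned to intervention and control areas using a 1:1 allocation ratio". The comparison therefore rests on 14 randomised units. By woman the arms are unequal: "277 women will be recruited for the intervention group and 413 women recruited for the control group".

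The analysis is given in one sentence of the Data analysis section, "We will use mixed-effect logistic regression to compare between the groups as the outcome", with adjustment for an open list of possible confounders. The article names no test statistic, reference distribution, degrees of freedom or effect measure.

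The target is stated three times:
- Abstract: "difference in percentage of cervical cancer screening uptake between the two study arms".
- Data analysis: "the primary outcome would be the difference in the proportion of women who participate in the cervical cancer-screening program between intervention and control within 1" (the quote stops before its unit, a year).
- Primary and secondary outcomes: "percentage change in cervical cancer screening uptake from baseline to follow-up in the intervention group compared to the control group".

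The first two are between-arm differences in a proportion. The third is a change from baseline compared between arms.

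**The concern.** Two features deserve attention.

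First, seven wards per arm leave 12 degrees of freedom for the between-ward variance. A Wald z test of a random-intercept logistic model treats that variance as known, and with so few wards it is often estimated as zero. The model then behaves as if women had been randomised individually. An uncorrected test would reject too often and its interval would be too narrow.

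Second, the arm coefficient of the model is a log odds ratio conditional on ward, while the outcome and the planned 10% gain are on the percentage scale. Without a stated conversion, the main result and its interval have no defined source.

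**Working it through.** **Inputs from the article.** 14 wards, 7 per arm; 277 and 413 women; ICC 0.01; 20% loss; 90% power; 49 women per ward; 690 in total; an effect of 10%, read here as percentage points.

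**Assumptions.** Two-sided 5% level. Control uptake is not given for the power calculation. The Background cites 2.8%, 1.5% and 5.4%, of which 5.4% (ages 30-65) is closest to the trial's age range. Uptake of 10% and 20%, and ICCs above 0.01, are included to show the range.

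**1. The plan's own sample size.** For 5.4% against 15.4%, the pooled two-proportion formula gives

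n = [1.96·√(2 × 0.104 × 0.896) + 1.2816·√(0.054 × 0.946 + 0.154 × 0.846)]² / 0.10² = (0.846 + 0.546)² / 0.01 ≈ 194 per arm.

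Solving 7m = n[1 + (m − 1) × 0.01] gives m = 194 × 0.99 / (7 − 1.94) = 38.0 analysed per ward. Then 38.0 / 0.8 = 47.4, so 48 per ward and 672 in total, close to the stated 49 and 690. A control uptake of about 5.7% matches; 10% would need about 76 per ward. The stated size therefore agrees with a normal-theory formula. That does not show which test will be used.

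**2. Type I error.** Data were simulated with no arm effect, 3,000 trials per scenario (Monte Carlo standard error about 0.4 points). After 20% loss there were 39 women analysed per ward, or 32 against 47 by arm (277/7 × 0.8 and 413/7 × 0.8). Uptake was 10% or 20%, with beta-distributed ward rates. The random-intercept logistic model, with arm only, was fitted by maximum likelihood with 21-point quadrature.

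| ICC | Wald z | same model, t on 12 df | ward-level t-test, 12 df | variance fitted as about zero |
|---|---|---|---|---|
| 0.01 | 6.2-7.2% | 3.6-4.6% | 4.5-5.0% | about 38% |
| 0.03-0.05 | 8.6-9.2% | 5.6-6.3% | 4.4-4.9% | 3-11% |
| 0.10 | 10.2-13.2% | 7.2-9.8% | 4.5-4.8% | under 1% |

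Smaller runs agree:
- Wards of 22-63 women, 2,000 trials: Wald z 6.4-7.0% at ICC 0.01 and 8.7% at 0.03 and 0.05.
- Normal random effects, as the model assumes, 1,000 trials: 6.6-6.8% at 0.01, 7.8% at 0.03 and 9.9% at 0.05.
- 32 against 47 women per ward, 800 trials: about 5-7% at 0.01 and 8-9% at 0.03-0.05.

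Across these runs the ward-level t-test stayed at about 3.5-6%. For orientation, P(|t₁₂| > 1.96) = 7.4%.

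**3. Effect scale.** A gain of 10 points corresponds to these odds ratios:

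| Control uptake | Odds ratio |
|---|---|
| 2.8% | (0.128/0.872)/(0.028/0.972) = 5.1 |
| 5% | 3.35 |
| 10% | 2.25 |
| 20% | 1.71 |

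An odds ratio alone does not give the stated outcome.

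**4. Cost of using t.** The critical value rises from 1.96 to 2.179, a factor of 1.11. With 49 × 0.8 = 39.2 analysed per ward, the design effect is 1 + 38.2 × 0.01 = 1.382, and the effective size per arm is 274.4 / 1.382 = 198.6. At 5.4% against 15.4% the standard error is √(0.1814/198.6) = 0.0302, so the standardised effect is 3.31. Power is 91% on z and 86% on noncentral t with 12 df. At 10% control uptake it is 80% and 74%. With the 277 and 413 split after loss, at 5.4%, it is about 89% and 83%.

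**The case against.** The strongest reply is that the inflation is attached to a test the article never names. It states a model class and a software package; the Wald z test is a reader's inference from common practice. Degrees of freedom and small-sample corrections are often left to a statistical analysis plan, which is not shown here. That stands: a reader might infer that the trial's false-positive rate exceeds 5%, but the documents support only a conditional statement.

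A reader might also infer that the planned analysis cannot produce the primary outcome. It can. Predictions from a logistic model can be standardised to a difference in proportions, and the Data analysis section names that difference in the same sentence as the model. The article never mentions an odds ratio. What remains is that the linking step is unstated.

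The excess is also modest at the only ICC in the article. Rates near 9% need an ICC three to five times larger, which the article does not suggest. The simulations have limits: no covariates, and in the main run equal ward sizes within arm. Its beta ward rates differ from the model's normal random effect and probably add to the excess at ICC 0.10; the run with normal effects still shows the excess at 0.01-0.05. A few fits with an undefined standard error were counted as non-rejections.

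The remedy has a price too. With a t reference, power falls below the claimed 90% at an assumed 5.4% control uptake.

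**Conclusion.** The point holds as a cheap improvement, not as something that must be fixed. With seven wards per arm, an uncorrected Wald z test of the named model would have a type I error of about 6-7% at the planned ICC and about 8-9% at 0.03-0.05. A ward-level t-test stays close to 5%. The article rules out neither a small-sample correction nor a standardised risk difference; it states neither. Replacing the stated method with one that holds its level and estimates the stated quantity directly is worthwhile. The sizes rest on the assumed uptake, ward sizes and larger ICCs.

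**What to change.** Make the primary analysis a comparison of ward uptake proportions, or of covariate-adjusted ward residuals, between arms by t on 12 degrees of freedom. Report the percentage-point difference with its 95% interval.

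Alternatively, keep the mixed logistic model, refer the arm effect to t on 12 degrees of freedom, and report the standardised risk difference with its interval. This largely restores the 5% level up to an ICC of about 0.05 but not fully beyond it: 7.2-9.8% at 0.10.

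In either case:
- Give the odds ratio as supportive.
- Reconcile the between-arm difference in the abstract and the Data analysis section with the change-from-baseline definition in the outcomes section. A comparison of follow-up ward proportions alone does not deliver the latter.
- Restate the 90% power on the t basis, with the assumed control uptake.

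The cost is a few sentences and a few lines of code, a critical value about 11% larger (2.179/1.96), and some 5 to 6 points of power in the scenarios shown. The Trial status section puts completion of the endpoint assessment at the end of August 2021, after the article's publication, so the wording could have been settled before the outcome data were complete.
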